### Interventions

Patients are randomised in a 1:1 ratio to receive one ultrasound-guided injection in each submandibular gland of ASCs or placebo. The injections are done without any anaesthesia or pain medications. ASCs are provided by the Cardiology Stem Cell Centre (CSCC) at Rigshospitalet. The donated adipose tissue will undergo a strict processing protocol for isolation of ASCs according to good manufacturing practice (GMP) in clean room facilities [18]. The cell products will come from a total of 4–5 healthy donors. Only one donor’s cells will be used in each cell vial. Placebo is consisting of CryoStor10 (BiolifeSolutions), the freeze media for ASCs containing 10% dimethyl sulfoxide (DMSO). The frozen suspension of ASCs or placebo will be thawed just before injection and 0.5 mL of ASC or placebo are injected into each submandibular gland. Patients receiving ASCs will receive a dose of 25 × 10^6^ cells per gland. Injections are carried out using a sterile 1 ml syringe and a sterile 23G (0.6 mm × 60 mm) needle on each side. A trained project nurse will thaw the frozen suspension of ASCs or placebo just before injection, and the syringes are covered in sterile green tape without information about the content of the syringes, to ensure that neither the patients nor the study staff can see the suspension injected. The injection of ASC or placebo is performed ultrasound-guided by free hand by a trained investigator (doctor) using a linear 9–18 MHz transducer. Patients are placed supine and the neck is slightly rotated and extended. The superficial part of the gland will be visualised, as being the part of the gland located between the digastric muscles and superficial to the mylohyoid muscle. The needle is placed in the gland from the anterior part towards the posterior, in a plane parallel to and superficially to the mylohyoid thus avoiding risk to the lingual artery. Injections are performed during a slow retraction of the needle placing the relevant volume in the gland.

### Outcomes

The primary endpoint is to evaluate the impact of ASC injections on unstimulated salivary gland function compared to placebo in patients with previous head and neck cancer. The change is evaluated from baseline to month four.

Secondary endpoints are as follows:

To compare the effect of ASC injection, relative to placebo, from baseline to month four on all of the following outcome measurements:Change in stimulated salivary gland function.Change in the patient-reported outcome of xerostomia: The European Organisation for Research and Treatment of Cancer Quality of Life Questionnaire, Head and Neck-35 (EORTC QLQ-H&N35):Domains for dry mouth (HNDR)Domains for sticky saliva (HNSS)Domains for swallowing (HNSW)Change in the patient-reported outcome of xerostomia: Xerostomia Questionnaire (XQ).Change in the composition of salivaSafety evaluated by the development of treatment-related adverse events, serious adverse reactions, or deathImmune response to allogeneic ASC measured by the development of de novo HLA

Tertiary outcomes are as follows:

The change in unstimulated whole salivary flow rate, stimulated whole salivary flow rate, patient-reported outcome of xerostomia evaluated by two questionnaires (EORTC QLQ-H&N35 and XQ), composition of saliva, safety, and immune response in patients receiving ASC injection compared to placebo is further evaluated at 12 months.

### Participant timeline

Patients who are interested in participating in the project will initially be contacted by phone by the investigators for inquiries about their interest in participating in the research project, and to clarify any initial questions. If patients are interested in participating in the project, they are invited to a screening visit at the Department of Otorhinolaryngology, Head and Neck Surgery, and Audiology, Rigshospitalet. Before the visit patients will receive written information regarding the study, the pamphlet “Forsøgspersoners rettigheder i et sundhedsvidenskabeligt forskningsprojekt” (“Rights of test subjects in a health scientific research project”) [19], and the pamphlet “Før du beslutter dig” (“Before deciding”) [20]. Patients are further informed that they have the right to bring a counsel to the screening visit.

The screening visit is conducted by the principal investigator or a trained sub-investigator (doctor). At the screening visit, patients will initially fill out a consent form. When the consent form is completed, inclusion- and exclusion criteria are reviewed with the patients. Patients will have their medical history evaluated, and undergo an ear, nose, and throat examination including an ultrasound exam of the submandibular salivary glands and the neck. If patients meet inclusion criteria so far, they will have whole saliva flow measured by sialometry (Supplementary 2), have blood samples collected and analysed for relevant kidney, infection, and liver parameters, s-HCG when relevant, and for the presence of HLA antibodies. Furthermore, patients will fill out QoL questionnaires (Supplementary 3). Saliva samples collected during the sialometry will be saved for chemical analyses and analyses of saliva composition (Supplementary 4). If patients are eligible for inclusion, they are randomised in a 1:1 ratio to receive ultrasound-guided injections of either ASCs or placebo in the submandibular glands no later than 90 days after the baseline visit. If patients fulfil one or more exclusion criteria they will not be included in the study hereafter and will not be randomised. Their data including the salivary samples will not be saved.

Patients are followed up after 4 month (+/− 14 days) and after 12 months (+/− 4 weeks). At the follow-up visits, patients will undergo saliva flow measurements, have analyses of saliva composition, have blood samples taken (for HLA antibodies), fill out QoL questionnaires, and have an ultrasound exam of the submandibular salivary glands. Lastly, all adverse events are monitored throughout the study period, from the time of treatment until the last day of follow-up (Fig. 1). When all study participants have completed the 4-month follow-up data will be unblinded. All data will be documented on-site in a secure web database, REDCap (Fig. 2).

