## Methods: assignment of interventions

### Allocation

A predefined randomisation code is established for all 120 patients according to patient treatment order (1–120) from the start of the trial. The randomisation is done randomly in a 1:1 ratio. The allocation sequence is generated using www.randomization.com. Randomisation is performed in blocks of six, three patients receiving ASCs and three patients receiving placebo to avoid clustering of treatments. Within blocks of six, a balanced use of donors will be applied. The randomisation is done by one person, the allocation manager, at the Cardiology Stem Cell Centre, CSCC, The Heart Centre, Rigshospitalet, and the staff involved in the trial is independent of the randomisation. The allocation manager will store the randomisation table, and the table with randomisation numbers will only be available to one specified person at the CSCC, The Heart Centre, Rigshospitalet, until the end of the trial. This person will not be involved in analysing data related to the study endpoints.

For the purpose of safety and potential unblinding, two sets of sealed envelopes containing the randomisation code for each patient are made. One envelope is locked up at the clinical site at the sponsor and is thereby available for the investigator, and one envelope is locked up at the CSCC production facility. The allocation envelopes will be monitored by the GCP unit during the trials to ensure that they are not opened before the end of the study.

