### Blinding

This is a double-blinded study. Both the sponsor, investigators, and study staff (except for staff involved in stem cell preparation and staff involved in bioanalytical analyses) and patients will be blinded to treatment assignment. Data analysts will further use a dataset where the groups are masked. The injection syringes of either ASC or placebo will be identical to ensure blinding.

Emergency unblinding can be performed at any time if it is considered necessary by the principal investigator or the sponsor. Participants are issued with “In case of emergency” cards to be carried at all times during the study including an emergency phone number. If the trial or a single subject is prematurely unblinded the principal investigator will document the reason for unblinding and notify the Danish Medical Agency and the National Ethics Committee.

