### Statistical methods

The analysis will be performed on the intention-to-treat population (ITT) and a statistical analysis plan will be completed before the end of the study. The primary endpoint is change in unstimulated whole saliva flow rate. The change in saliva flow rate from baseline to 4-month follow-up visit will be presented as change in mL/min and percentage change. The secondary endpoint of stimulated whole salivary flow rate will also be presented as change in mL/min and percentage change. Patient-reported outcome measurements will be evaluated as the changes from baseline to the 4-month follow-up visit and will be presented as a summary score ranging from 0 to 100. An ANCOVA model will be used to analyse continuous outcome measures (change from baseline). The baseline value will be included as a continuous covariate and the randomised treatment group will be included as a categorical variable. Data will be analysed after all patients have completed their 4-month follow-up time, and after the 12-month follow-up time.

Upon completion of the 4-month follow-up visit for all patients, the data will be unblinded, and an analysis of the 4-month follow-up data will be conducted. Subsequently, the long-term follow-up analysis will take place once all patients have completed their 12-month follow-up.

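### Data are to be unblinded after month 4, but the allocation rules keep the code closed to the end of the trial, and nothing secures the blind for the 12-month assessments

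*Protocol article*

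**What the plan says.** All references are to the protocol article.

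- **When the data are unblinded.** Participant timeline: "When all study participants have completed the 4-month follow-up data will be unblinded". Statistical methods gives the same trigger, attaches the 4-month analysis to it, and continues: "Subsequently, the long-term follow-up analysis will take place once all patients have completed their 12-month follow-up".
- **How long the code stays closed.** Under Allocation, the table of randomisation numbers "will only be available to one specified person at the CSCC, The Heart Centre, Rigshospitalet, until the end of the trial". That person takes no part in analysing endpoint data. Two sets of sealed envelopes exist, and the GCP unit monitors them "to ensure that they are not opened before the end of the study".
- **Who is blinded.** Blinding covers the sponsor, investigators, patients and most staff, and gives analysts a dataset with masked groups. It states no end date. The abstract adds that personnel who are unblinded take no part in assessing outcomes.
- **What is still to come at month 12.** Outcomes lists both flow rates and both questionnaires as tertiary outcomes, and adds: "composition of saliva, safety, and immune response in patients receiving ASC injection compared to placebo is further evaluated at 12 months".
- **Who collects it.** Data collection methods assigns the 12-month visit to the principal investigator or a sub-investigating doctor. Access to data gives these same roles the full dataset while the trial runs. Harms has them examine new medical events at follow-up visits.

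**The concern.** The two sets of rules cannot be followed together as written. If the table stays with one non-analysing person until the trial ends, nobody else can unblind the data at month 4. If the data are unblinded at month 4, that restriction has lapsed about eight months before the last visit.

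The 12-month comparison is at stake. Follow-up has only two time points, so month 12 is the trial's only evidence on whether an effect lasts. The most exposed outcomes are the questionnaires, which patients complete themselves, the sialometry run by the investigators, and the attribution of adverse events to treatment. Saliva composition and HLA antibodies are laboratory measures and are less exposed. Late recruits could also be assessed at month 12 under different conditions from early recruits, within a trial reported as double-blind.

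**Working it through.** The plan states no figure on this point, so there is none to reproduce. The check has two parts.

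**1. The rules side by side**

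- *Does the trial end at month 4?* No. Trial status expects the last visit in February 2024, and Harms treats the study period as 12 months. The pregnancy exclusion criterion speaks of a 4-month study period, but only there.
- *Table.* One person holds it to the end and does not analyse endpoints. An unblinded 4-month analysis needs someone else to have the code. This is a direct conflict.
- *Envelopes.* They exist for safety and possible unblinding. They could stay sealed while group labels are released another way, so this is a tension rather than a strict contradiction.
- *Assessors.* The abstract bars unblinded personnel from outcome assessment. If allocation enters the dataset after month 4, the people who collect the 12-month data have access to it. Nothing says that this access is then restricted.

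**2. How many 12-month visits follow unblinding**

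Inputs: recruitment from February 2021 to February 2023, about 24 months (Trial status); 120 patients; visits at 4 months ± 14 days and 12 months ± 4 weeks; injection up to 90 days after baseline (Participant timeline). Even accrual is my assumption.

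- Unblinding falls at 24 + 4 = 28 months from the start, about June 2023.
- A patient treated at month t has the 12-month visit after unblinding if t + 12 > 28, that is, t > 16.
- Share exposed: (24 − 16)/24 = 8/24 = 33%, and 120 × 8/24 = **40**.

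Varying the inputs separately:

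| Variation | Calculation | Visits after unblinding |
|---|---|---|
| Last month-4 visit 0.5 month late, 12-month visits 1 month early | 120 × (8 − 0.5 − 1)/24 | 32.5 |
| Last month-4 visit 0.5 month early, 12-month visits 1 month late | 120 × (8 + 0.5 + 1)/24 | 47.5 |
| Every patient injected 3 months after baseline | delay cancels: 120 × 8/24 | 40 |
| Only the last patient injected 3 months after baseline | 120 × (8 − 3)/24 | 25 |
| As the row above, with 25 months of accrual | 120 × (8 − 3)/25 | 24 |

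The range is therefore about 24 to 48, or 20% to 40% of 120. Stacking the least exposed options would go lower still: 120 × (8 − 3 − 0.5 − 1)/24 = 17.5. The expected last visit in February 2024 fits a last injection near February 2023, which supports the central figure.

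Sample size expects about 20% dropout. If that applied in full by month 12 and equally to late recruits, 40 × 0.8 = 32 visits, with a range of 24 × 0.8 = 19 to 48 × 0.8 = 38.

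**The case against.** The strongest reply is that releasing group labels after a completed primary analysis, as disclosed here, is not wrong in itself, and that this reading assumes who will learn the allocation. Much of that stands.

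- **A reader might infer that investigators and patients will be told their allocation, so that the 12-month comparison is biased.** The text says only that data will be unblinded; no section says that individual codes go to patients or assessors. The full dataset access is a general statement about the trial, during most of which allocation is not meant to be in the data. Bias is a risk, not a certainty.
- **A reader might infer that there is no firewall.** The abstract states one, and Blinding has no end date. What is missing is any rule carrying these through once the data are unblinded.
- **A reader might want the bias expressed in questionnaire points.** The article gives no basis for the shift that knowing the allocation would cause, so any such figure would only restate an assumption.
- **A reader might think the main result is compromised.** The primary and secondary comparisons are at month 4 and are complete before unblinding. Under even accrual, about two thirds of 12-month visits also precede it.
- **Two supporting points are limited.** The sialometry method is in a supplement not at hand, so how far knowledge of allocation could influence it is a judgement. Safety data after month 4 are described inconsistently: Participant timeline has all adverse events monitored to the end of follow-up, while Harms has only serious ones after month 4. Some safety data follow unblinding under either description.

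It can also be said that detailed unblinding roles belong in the full protocol or the analysis plan. Their absence here would be no finding. The conflict between two rules that the article does state is one.

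**Conclusion.** The point holds, at moderate severity. The month-4 unblinding conflicts directly with the rule on the randomisation table and sits badly with the rule on the envelopes, so the GCP unit is asked to monitor a restriction that other sections appear to override. Followed as written, the plan also lets those who collect the 12-month data reach the allocation, against the article's own bar on unblinded assessors.

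The exposure is confined to tertiary 12-month outcomes at visits after unblinding: about 40 of 120, range about 24 to 48, and about 32 if the full 20% dropout applies. These counts rest on even accrual, the stated recruitment dates and unblinding as soon as the last month-4 visit is done; a later unblinding would lower them. They count visits at risk, not visits shown to be biased. The direction and size of any bias cannot be derived from the article.

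**What to change.** Reconcile Participant timeline and Statistical methods with Allocation and with the abstract's bar on unblinded assessors. State that after the 4-month lock only a statistician outside the clinical team receives the code and reports group-level results. Patients, 12-month assessors and those judging adverse events stay blinded to individual allocation until the 12-month data are locked. Give Blinding that end date, and reconcile the two descriptions of adverse event monitoring after month 4.

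The article appeared in September 2023, after the projected June 2023 unblinding, so this may come too late; the article does not say whether codes have been released. If they have, record the date, describe later 12-month visits as not blinded, and add a sensitivity analysis restricted to 12-month visits made before it. Allocation followed treatment order in blocks of six, so a cut by calendar date should leave the arms close to balanced.

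The cost is wording, an access restriction in REDCap, and individual allocation disclosed up to about eight months later (12 − 4). The sensitivity analysis would keep about 120 − 40 = 80 patients (72 to 96) before dropout. With equal outcome variance, its standard error would be about √(120/80) = 1.22 times that of the full 12-month analysis.

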**Fig. 1 Fig1:**
[figure not shown]
Flowchart of study design. Abbreviation: ENT, ear-nose-throat; QoL, quality of life

**Fig. 2 Fig2:**
[figure not shown]
SPIRIT figure

### Sample size

From our previous study MESRIX-I we assess to increase saliva production for whole unstimulated whole saliva flow rate (in ml/min) by about 33% or in absolute numbers from 0.125 to 0.155 after 4 months. The power calculation is based on a power of 0.8 and an alpha of 0.05. This means that the total number of patients included would have to be 100 (50 in each group). We expect a dropout rate of about 20% and therefore aim to include 120 participants in total.

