With the aim of restoring the salivary gland function in patients suffering from xerostomia due to radiotherapy, we have completed a randomised, placebo-controlled pilot study with 30 patients evaluating the safety and efficacy of ex vivo expanded autologous adipose-derived mesenchymal stem cells (ASCs) for radiation-induced xerostomia [13, 14]. This study showed that the treatment was safe without any serious adverse events. Also, patients treated with autologous ASCs had an increase in saliva production of 33–50%, and compared to the placebo group the patients treated with ASC experienced a significant improvement in their QoL as evidenced by reduced difficulties in eating [14]. However, we observed a substantial individual variation in ASC manufacturing in regard to cell yield, cell quality, and expansion time. We thus recently investigated the safety of allogeneic ASCs for the treatment of xerostomia in a clinical safety and feasible trial [15], including ten patients who received intraglandular injections of allogeneic ASCs. No serious adverse reaction occurred, and the efficacy data was similar to the results from our first trial with autologous ASCs with an increase in saliva production of 46% after 4 months. Patients also gained vital QoL measures regarding dry mouth, sticky saliva, and swallowing [15].

The purpose of this study is to assess the efficacy and safety of treatment with ASCs from healthy donors on radiation-induced salivary gland hypofunction and xerostomia in previous head and neck cancer patients in a randomised, double-blinded, placebo-controlled trial.

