### Objectives

The trial aims to evaluate the effectiveness and safety of treatment with ASCs, as compared to a placebo in patients with radiation-induced salivary gland hypofunction.

The primary research hypothesis is as follows: Does treatment with ASCs, as compared to a placebo, lead to improvements in unstimulated whole salivary flow rate in patients with radiation-induced salivary gland hypofunction?

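### The planning effect is given as about 33%, but 0.125 to 0.155 mL/min is a 24% rise, so the stated 80% power fits only one of the two figures; the placebo change assumed is not stated

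*Protocol article*

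**What the plan says.** The Sample size section of the protocol article takes its effect from the sponsor's pilot: "From our previous study MESRIX-I we assess to increase saliva production for whole unstimulated whole saliva flow rate" "by about 33% or in absolute numbers from 0.125 to 0.155 after 4 months". It continues: "The power calculation is based on a power of 0.8 and an alpha of 0.05", and concludes that "the total number of patients included would have to be 100 (50 in each group"). An allowance for dropout then brings the total to 120.

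The Background and rationale section describes the pilot as randomised and placebo-controlled with 30 patients, and reports that "patients treated with autologous ASCs had an increase in saliva production of 33–50" percent. The comparison with placebo in that sentence concerns quality of life; no placebo-arm flow rate is given.

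The Objectives section asks: "Does treatment with ASCs, as compared to a placebo, lead to improvements in unstimulated whole salivary flow rate". The Outcomes section likewise defines the primary endpoint against placebo, from baseline to month 4. The Statistical methods section analyses change from baseline by ANCOVA, with baseline as covariate and treatment group as factor.

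**The concern.** Two features of the sample-size sentence do not fit.

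- **The percentage and the absolute values disagree.** They are joined by an *or*, as two expressions of one effect, yet they lie 0.011 mL/min apart (0.04125 − 0.030), which is more than a third of the smaller one. The 80% power at 50 per group can hold for one of them but not for both.
- **The effect is worded as a change over time, not as a difference between arms.** It is a rise from a starting value to a 4-month value. The trial tests ASC against placebo, so the quantity that drives power is the ASC change minus the placebo change.

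At stake is how the primary result will be read. When the 4-month analysis is reported, the observed difference and its confidence interval will be set against the effect the trial was planned to detect. A reader of the article cannot say whether that is 0.030 or 0.041 mL/min, or what placebo change it allows for.

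**Working it through.** **Inputs.** From the Sample size section: 0.125 and 0.155 mL/min, about 33%, power 0.80, alpha 0.05, 50 per group. Allocation is 1:1 (Allocation section). Assumptions made here: a two-sided test, because sidedness is not stated, and a two-sample t-test without baseline adjustment. The article gives no SD, so the plan's figure of 100 cannot be reproduced directly; the SD has to be solved backwards.

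**Step 1: the percentage.**
- (0.155 − 0.125) / 0.125 = 0.030 / 0.125 = 24.0%.
- A 33% rise: 0.125 × 0.33 = 0.04125 mL/min, ending at 0.125 × 1.33 = 0.166 mL/min.
- Rounding cannot explain the gap. The extremes are (0.1545 − 0.1255) / 0.1255 = 23.1% and (0.1555 − 0.1245) / 0.1245 = 24.9%.
- Dividing by the end value gives 0.030 / 0.155 = 19.4%, which is further from 33%.

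**Step 2: what 50 per group implies.** For a t-test with 50 per group, 80% power needs a standardised difference d = 0.566. The implied SD is difference / d:
- if 0.030 was used: 0.030 / 0.566 = 0.053 mL/min;
- if 33% was used: 0.04125 / 0.566 = 0.073 mL/min.

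**Step 3: power for each effect under each implied SD, 50 per group.**

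| Effect used in planning | Implied SD | Power for 0.030 | Power for 0.04125 | Per group needed for the other effect |
|---|---|---|---|---|
| 0.030 (24%) | 0.053 | 80% | 97% | 27 |
| 0.04125 (33%) | 0.073 | 53% | 80% | 94 |

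The normal approximation gives nearly the same results (SD 0.0535 and 0.0736; 27 and 95 per group).

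**Step 4: the placebo change.** The expected contrast is the ASC rise minus the placebo change. Take SD 0.053 and an ASC rise of 0.030. The placebo changes below are illustrative assumptions; the article reports none.

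| Assumed placebo change (mL/min) | Expected difference | Power, 50 per group |
|---|---|---|
| −0.010 | 0.040 | 96% |
| 0 | 0.030 | 80% |
| +0.005 | 0.025 | 65% |
| +0.010 | 0.020 | 46% |

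The stated power therefore corresponds to the trial's contrast only in the zero row. A placebo rise lowers it and a placebo fall raises it. The difference that the trial can detect depends on n and SD and does not move with the placebo change; what moves is the difference to be expected.

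**The case against.** The best defence is that the only absolute planning values in the article are 0.125 and 0.155 mL/min, and that the primary endpoint is presented in mL/min. The natural reading is then a planned difference of 0.030, with the percentage a loose label echoing the lower end of the range in the Background. The rival end value of 0.166 appears nowhere in the article. This is a fair reading and may well be the right one. But the text presents the two figures as equivalent, so one of them is wrong as written, and the article alone does not settle which was entered in the calculation.

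A mean of individual percentage changes can also be 33% while group values rise by 24%. That is possible, but the section does not say it.

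On the placebo arm, assuming no change is a common simplification in an established condition; entry requires two years of follow-up without recurrence. The pilot had a placebo arm, so its change may already have been considered. What stands is narrower: the assumption is unstated. Nothing in the article shows it to be wrong.

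The absent SD is not itself a fault. The article condenses a fuller protocol, which may give it. That document could show which effect was used, but it could not make 0.125 to 0.155 a 33% rise.

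Finally, the analysis is an ANCOVA. If the planning SD was not adjusted for baseline, the true power may be higher than a t-test gives. That softens the size of the power losses above but leaves the inconsistency in place.

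**Conclusion.** The inconsistency is certain: 0.125 to 0.155 mL/min is 24%, not about 33%, and no rounding or change of denominator bridges the gap. The consequence depends on which figure was used. If it was 0.030, the percentage is a wrong label and a true 33% rise would have about 97% power. If it was 0.041, power for the stated 0.030 is about 53%. Both results rest on back-solved SDs (about 0.053 and 0.073), a two-sided alpha and an unadjusted t-test.

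The effect is also worded as a 4-month rise, and equals the ASC-versus-placebo contrast only under an unstated assumption of zero placebo change.

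A reader might infer that the trial is underpowered or that 100 patients are too few. The article does not support that: without the SD it cannot be shown. Nor would it be right to infer that any placebo change weakens the trial, since only a rise narrows the expected difference, or that a null result could not be interpreted. A confidence interval in mL/min can be compared with 0.030, and with 0.041 as well. The estimand, the analysis model and the type I error are unaffected.

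Severity is moderate: a correction to the sample-size statement.

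**What to change.** In the Sample size section:

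1. Keep the one effect that was actually used and correct the other figure: either 33% becomes 24%, or 0.155 becomes 0.166 mL/min. If the percentage is a mean of individual changes, say so.
2. Express the effect as an ASC-minus-placebo difference in mL/min at 4 months, and state the placebo change assumed. The pilot's placebo arm is the obvious source. Giving the SD alongside would let a reader reproduce the 50 per group.
3. Restate the power for the number enrolled.

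The cost is one rewritten paragraph. The Trial status section says recruitment finished in February 2023, and no further recruitment or change to the analysis is needed. The downside is that the stated power may become less favourable. The correction is best made before the primary result is interpreted, so that the planned effect is not chosen with the data in view.

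### Enrolling 120 at 20% dropout leaves 96 evaluable patients, four short of the plan's own target of 100 (minor)

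*Protocol article*

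**What the plan says.** All the inputs are in the protocol article, section Sample size. The design values are stated as "The power calculation is based on a power of 0.8 and an alpha of 0.05", and the result is that "the total number of patients included would have to be 100 (50 in each group"). The next sentence adds the dropout allowance: "We expect a dropout rate of about 20% and therefore aim to include 120 participants in total".

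The same total appears in the Abstract (60 per arm) and in Allocation (a randomisation list numbered 1 to 120). No other section gives a different dropout rate or another route from 100 to 120.

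Three other statements bear on the size of the problem:

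- The target effect is an increase "by about 33% or in absolute numbers from 0.125 to 0.155 after 4 months" (Sample size).
- "Randomisation is performed in blocks of six, three patients receiving ASCs and three patients receiving placebo" (Allocation).
- "The analysis will be performed on the intention-to-treat population (ITT"), using ANCOVA with the baseline value as covariate (Statistical methods).

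Trial status reports that recruitment had finished by February 2023.

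**The concern.** The protocol presents 120 as following from 100 and a 20% loss. It does not follow. Adding 20% to the number needed at the end differs from enrolling enough that 100 remain after 20% are lost, because the loss applies to the larger, enrolled number.

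What is at stake is the justification of the primary-endpoint sample size. A reader of this section would believe that the trial can lose one patient in five and still have its 100. It can lose only one in six. If the sentence is carried into the results paper, observed attrition will be judged against the wrong tolerance.

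**Working it through.** **Inputs (all from Sample size unless noted)**

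- Number needed: 100, that is 50 per group
- Expected dropout: about 20%
- Planned enrolment: 120, that is 60 per group
- Power 0.80 and alpha 0.05; sidedness not stated
- Effect in absolute terms: 0.155 − 0.125 = 0.030 mL/min
- SD: not stated
- Blocks of six, 1:1 (Allocation)

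**Step 1. Reproduce the stated figure.** 100 × (1 + 0.20) = 120. This matches exactly, so the allowance was applied as a multiplier on the number needed.

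**Step 2. Correct inflation.** N = n / (1 − dropout) = 100 / 0.80 = 125. Equal groups need 50 / 0.80 = 62.5, rounded up to 63 per group, so 126 in total. That is also 21 complete blocks of six, and 126 × 0.80 = 100.8 evaluable.

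**Step 3. Forward check of the plan.** 120 × 0.80 = 96 evaluable, 48 per group. The shortfall is 100 − 96 = 4 patients.

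**Step 4. Dropout that 120 can absorb.** 1 − 100/120 = 16.7%.

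**Step 5. Conditional power.** The 100 cannot be re-derived without an SD. To gauge the loss, assume that 50 per group gives exactly 80% power in a two-sided, unadjusted comparison of means.

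- Standardised effect (normal approximation): d = (1.960 + 0.842) / √(50/2) = 2.802 / 5 = 0.560. For a difference of 0.030 this implies an SD of 0.030 / 0.560 = 0.054 mL/min.
- Power at 48 per group: Φ(0.560 × √(48/2) − 1.960) = Φ(2.745 − 1.960) = Φ(0.785) = 78.4%.
- The exact t-test version gives d = 0.566, an implied SD of 0.053 and 78.3% power. A one-sided test (normal approximation) gives 78.6%.

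Once 50 per group is taken as exactly 80%, this loss does not depend on the SD or the effect. Under the same assumption (normal approximation, two-sided):

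| Dropout | Evaluable of 120 | Power |
|---|---|---|
| 15% | 102 | 80.8% |
| 16.7% | 100 | 80.0% |
| 18% | 98.4 | 79.4% |
| 20% | 96 | 78.4% |
| 25% | 90 | 75.7% |

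**Step 6. Possible gain from ANCOVA.** Suppose the 50 per group ignored baseline adjustment. Adjustment with within-arm correlation r between baseline and the analysed outcome multiplies the residual variance by 1 − r². Returning 48 per group to 80% needs 1 − r² = 48/50, so r = √0.04 = 0.2. At r = 0.3, power at 48 per group is 82.0% (t-test version). The document gives no value for r.

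**The case against.** The arithmetic is not in dispute. The case on the other side concerns what follows from it, and much of that stands.

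- **The dropout rate is approximate.** The text says about 20%, and 16.7% would make 120 exactly enough. That is possible as loose wording. But 120 is precisely 100 × 1.20, which points to the formula rather than to rounding, and the sentence as written still promises the wrong tolerance.
- **A reader might infer that the trial falls below 80% power, or has 78%.** The document does not support that as a flat statement. It gives no SD and no sidedness, and it does not show whether 100 is a calculated or a rounded figure. If the calculation gave 48 per group (implied SD about 0.052) and was rounded up to 50, 96 evaluable would still give 80%. The planned effect is also described in two ways: 0.030 is 24% of 0.125, whereas 33% of 0.125 is about 0.041. With the same back-solved SD, 48 per group would have about 97% power for 0.041. This objection stands, so the 78% is conditional.
- **The planned analysis is ANCOVA.** Even a modest baseline correlation would offset the loss. This stands as a possibility, not as proof of adequacy, because the correlation is unknown and the sample size section takes no credit for it.
- **Intention-to-treat keeps all 120.** This does not help. Naming the population does not supply missing 4-month flow rates, and the plan itself treats dropout as lost information by inflating for it.
- **The 100 could be the number enrolled.** The next sentence adds the dropout allowance on top of 100, which rules this out.

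Nor does the shortfall add uncertainty to the planning effect. A fixed deficit in numbers leaves the assumed effect as certain or uncertain as it was.

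**Conclusion.** The point holds as a minor arithmetic error. What is certain from the document alone is that, at the stated 20% dropout, 120 randomised gives 96 evaluable and not 100, that 100 would need 125 (126 in complete blocks), and that 120 covers dropout only up to 16.7%.

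The power consequence is small and conditional: a loss of under two percentage points, to about 78%, if 50 per group is exactly 80% in a two-sided unadjusted t-test. The planned analysis may lose nothing. The estimand, the analysis and the conduct of the trial are unaffected.

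**What to change.** Recruitment is closed and the allocation list is fixed at 120, so no design change is proposed. Replace the dropout sentence, in the protocol and wherever it is carried forward, with wording such as:

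> 120 randomised leaves 96 evaluable at 20% dropout; the target of 100 evaluable is met only if dropout is at most 16.7%.

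Do not add a power figure for 96 patients unless the SD, the effect in mL/min, the sidedness and the test (unadjusted or baseline-adjusted) are stated with it.

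The cost is one sentence. The stated dropout tolerance becomes slightly less favourable, and no procedure or analysis changes.
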